| Inclusion            | Criteria include: Newly diagnosed with breast cancer (i.e. prior to surgery), scheduled for breast cancer surgery at Section of Breast Surgery at Rigshospitalet, 18 years or above, Danish citizen, read, understand and speak Danish, female gender, no severe cognitive problems or dementia, no severe psychiatric disease requiring treatment, e.g. schizophrenia, alcohol or narcotic dependence, has signed written informed consent. Those who experience high psychological distress (score $\geq 7$ on the distress thermometer) will enter the RCT whereas those who experience low psychological distress (score $< 7$ on the distress thermometer) will be followed in an observational questionnaire study. |
| Method               | During a 2-year period, 758 patients newly diagnosed with breast cancer will be recruited from the Section of Breast Surgery at Rigshospitalet, Copenhagen. Of these 324 participants enter the RCT and are randomized in a computer-generated sequence of 1:1 to the intervention (nurse-navigation) or control group (standard care). A total of 432 participants will enter an observational questionnaire study. All participants are followed for 1,5 years.                                                                                                                                                                                                                                                         |
| Intervention         | The intervention is a program of individually tailored nurse navigation for distressed breast cancer patients. The specific change objectives are to improve knowledge, social norms and self-efficacy so that the patient can self-manage or actively engage in professional rehabilitation to alleviate her psychological and physical symptoms. The intervention consists of systematic report of symptoms to the nurse and up to six individual, manual-based, face-to-face or telephone nurse navigator sessions depending on individual needs.                                                                                                                                                                      |

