### ***Randomization***

Women who are distressed (score  $\geq 7$  on the distress thermometer) (N=324) will be included in the randomized controlled trial and randomized in a computer-generated sequence of 1:1 to the intervention or control group, with stratification by age ( $< 60$  and  $> 60$  years), generating a balanced number of random assignments to the two groups in blocks of randomly varying sizes of six, eight or ten patients securing an equal distribution of patients in both groups. The randomization is blinded. Thus, neither the investigators nor the patients can influence the group to which each patient is allocated. An electronic platform will be developed by an experienced IT consultant company, to register, randomize and track included patients. The same platform will be used for the intervention activities and data collection.

Immediately after randomization, the nurse will inform patients about group allocation and consequences for further study participation. The nurse will schedule the first appointment with the patients in the intervention group.

Women who are not distressed (score  $< 7$ ) (N=432), will participate in an observational group following the same procedure as the control group.

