| Neuropathy         | Single items            | X                       |                  |                   |                   | X                  | X                   | X                   |

|                    |              |   |  |  |  |   |   |   |
|--------------------|--------------|---|--|--|--|---|---|---|
| Sleep              | PSQI         | X |  |  |  | X | X | X |
| Cognitive function | FACT-cog     | X |  |  |  | X | X | X |
| Health behavior    | Single items | X |  |  |  |   |   | X |
| Need for support   | Single items | X |  |  |  | X | X | X |
| Quality of life    | EQ-5D        | X |  |  |  |   |   | X |
| Acceptability      | Single items |   |  |  |  |   |   | X |

Note. MOS Medical Outcomes Study Social Support Survey (17). DT Distress thermometer (18,19). GAD 7 Generalized Anxiety Disorder (20). PHQ 9 (depression) The Patient Health Questionnaire (21). FACT-B Functional Assessment of Cancer Therapy –Breast (22). Physical Function Scale (29). PAM Patient Activation Measure (23). CARQ Fear of Recurrence (24). Pain (single items), neuropathy (single items). PSQI Pittsburgh Sleep Quality Index (25). FACT-cog Functional Assessment of Cancer Therapy-Cognitive (26). Health behavior including smoking, alcohol, physical activity, BMI (single items). Need for support (single items). EQ-5D Euro Quality of Life-5-Dimensional Classification (27).

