## STATISTICAL ANALYSES

Descriptive analyses will provide information on inclusion, feasibility, including participation in intervention components and data collection, satisfaction with the intervention, and information on nurse management of symptoms from medical records. Analyses will be based on intention-to-treat, with t tests to compare mean differences in change in each group between baseline and 6, 12 and 18 months of follow-up and with mixed models including all follow-ups. Primary analyses will test the effect of the intervention on distress, and secondary analyses will test for psychological symptoms, physical symptoms, and health behaviour (smoking, alcohol, BMI, physical activity). The effect of the intervention in the control and the intervention group will be assumed to be normally distributed and will be tested by the F-test. In all analyses, 99% confidence intervals will be calculated. Analyses will be performed based on the intention to treat principle including all participants and in sensitivity analyses, imputations of missing data will be performed using the last-observation-carried-forward method (28). In analyses aiming to describe the clinical impact of the intervention, we will estimate how many percent of the cases of distress, anxiety, depression and physical symptoms in the intervention versus the control group will be moved to non-cases. Furthermore, in cost-utility analyses, we will apply quality adjusted life years (QALY) to weigh the life expectancy of a patient against the Euro Quality of Life 5-Dimensions Classification (5Q-5D). Using incremental analyses, mean differences in costs (health care +disability + productivity loss + intervention) are compared with mean differences in health consequences for the intervention versus the control group.

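### The cost-utility comparison names no adjustment for baseline EQ-5D or the age stratum, although both are available and adjusting would sharpen the incremental QALY

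*Protocol*

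**What the plan says.** In the Statistical Analyses section the economic evaluation takes two sentences. The first gives the effect measure: "we will apply quality adjusted life years (QALY) to weigh the life expectancy of a patient", using EQ-5D. The second gives the comparison: "mean differences in costs (health care +disability + productivity loss + intervention) are compared with mean differences in health consequences for the intervention versus the control group". No covariate or model is named, and the construction of the QALY is not described.

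Three other places bear on the point:

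- Figure 2 schedules EQ-5D at two times only, before surgery and at 18 months: "Quality of life | EQ-5D | X | | | | | | X".
- The Randomization section has women "randomized in a computer-generated sequence of 1:1 to the intervention or control group", "with stratification by age", with the cut at 60 years.
- The Synopsis gives the horizon: "All participants are followed for 1,5 years".

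For the symptom outcomes, the same analysis section plans t tests on change from baseline and mixed models over all follow-ups. Baseline is therefore used explicitly there.

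**The concern.** The symptom comparisons are worded as differences in change from baseline. The cost-utility comparison is worded only as mean differences between arms. An analyst who follows the text literally would subtract arm means of QALYs and of costs and use neither the baseline EQ-5D nor the stratification factor.

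This matters more for a QALY than for most outcomes. If the QALY is the area under the utility curve, the pre-randomisation EQ-5D is itself part of the outcome. With only two measurement times it is half of it. A chance difference in baseline utility between arms then enters the QALY difference directly, and again through its correlation with the 18-month value. The age stratum is a lesser matter: where a stratification factor predicts the outcome, leaving it out of the analysis gives intervals wider than the design has earned.

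At stake is the precision of the incremental QALY in the planned cost paper (Paper 4 under Dissemination). Under Perspectives, promising cost-effectiveness is one of the conditions for offering implementation support to other departments.

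**Working it through.** **The plan's own figures.** The protocol states no QALY, EQ-5D or cost figure to reproduce. Its power figure for distress (61% against 81%, 130 per group, alpha 1%, stated 84%) reproduces at 84.2% with a two-sided two-proportion calculation, but it does not bear on this point. It supplies only the sample size: 324 × 0.8 = 259.2, which the protocol gives as 260, or 130 per arm.

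**Inputs from the protocol.** Horizon 1.5 years (Synopsis); EQ-5D at baseline (U0) and 18 months (U18) (Figure 2); n = 130 per arm (Power and participation); 99% confidence intervals (Statistical Analyses).

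**Assumptions, not in the protocol.** EQ-5D SD σ = 0.20 at both times (range 0.15 to 0.25); correlation ρ between U0 and U18 of 0.3, 0.5 or 0.7.

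**Construction A: two-point area under the curve.**

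- QALY = 1.5 × (U0 + U18)/2 = 0.75 × (U0 + U18).
- Unadjusted variance per woman = 0.75² σ² × 2(1 + ρ).
- Variance after adjusting for U0 = 0.75² σ² × (1 − ρ²).
- Variance ratio = (1 − ρ²)/[2(1 + ρ)] = (1 − ρ)/2, which does not depend on σ. The SE ratio is its square root.
- The SE of the arm difference is the per-woman SD × √(2/130).

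**Construction B: only U18 enters the QALY.** The variance ratio is 1 − ρ², so the SE ratio is √(1 − ρ²), whatever weight U18 carries.

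| ρ | SE unadjusted (A, σ = 0.20) | SE adjusted (A, σ = 0.20) | SE ratio, A | SE ratio, B |
|---|---|---|---|---|
| 0.3 | 0.030 | 0.018 | 0.59 | 0.95 |
| 0.5 | 0.032 | 0.016 | 0.50 | 0.87 |
| 0.7 | 0.034 | 0.013 | 0.39 | 0.71 |

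A simulation of 4,000 trials per value of ρ under construction A gave SE ratios of 0.58, 0.51 and 0.39, in agreement with the formula.

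**Interval width (A, ρ = 0.5, σ = 0.20).** The 99% half-width falls from 2.576 × 0.0322 = 0.083 to 2.576 × 0.0161 = 0.042 QALY.

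**Chance baseline gap (A).**

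- The SE of the baseline utility difference is 0.20 × √(2/130) = 0.025.
- A gap of that size adds 0.75 × 0.0248 = 0.019 QALY directly (0.014 to 0.023 for σ from 0.15 to 0.25).
- Counting its expected carry-over to 18 months, the factor is 0.75 × (1 + ρ). At ρ = 0.5 that is 1.125 × 0.0248 = 0.028 QALY.

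**Costs and age.** The protocol gives no cost SD, no relation of age to cost or utility, and no pre-randomisation cost measure. No gain can be computed for these.

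**The case against.** The strongest reply is that the protocol nowhere writes raw or unadjusted. Mean differences is a generic description of an incremental analysis, and regression-adjusted differences fit it equally well. Covariates and QALY construction for a secondary economic analysis are ordinary content of a statistical or health-economic plan, which may exist and is not shown. This stands in part. A reader might infer that the protocol commits to raw arm means, and the text does not support that. What remains is that the section does state a comparison. It names no covariate there, while its symptom analyses say explicitly that baseline is used. The literal reading is therefore the less efficient one.

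Second, the size depends on a QALY construction that the protocol does not give. This stands. With only the 18-month value in the QALY and ρ = 0.3, the SE falls by under 5%. Precision still improves under either construction at any positive correlation.

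Third, chance imbalance is ordinary sampling error, already reflected in the planned 99% intervals. That is correct: the unadjusted contrast is not biased, and the loss is one of precision. Stratified blocking also limits age imbalance by design.

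Fourth, a reader might infer that the cost difference is needlessly imprecise too, or that cost per QALY decides roll-out. The document supports neither. It has no figures from which to judge a cost-side gain, and Perspectives also requires positive effects of statistical and clinical significance.

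**Conclusion.** The point holds as a matter of efficiency in a secondary analysis. As worded, the cost-utility comparison names no adjustment, and the data for a better estimator are already in the design. If it is carried out unadjusted, the SE of the incremental QALY is 1.7 to 2.6 times what adjustment would give under the two-point area under the curve (1/0.59 to 1/0.39), and about 1.05 to 1.4 times if only the 18-month value enters (1/0.95 to 1/0.71).

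These figures assume ρ of 0.3 to 0.7 and, for the two-point version, equal SDs at both times. The absolute SEs also assume σ = 0.20 and 130 women per arm. The result is not a claim of bias, nor a finding that the protocol prescribes raw means. It makes no quantified claim about costs or about age. The change is worth making before the comparative analysis is run.

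**What to change.** In the Statistical Analyses section, state that:

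- the incremental QALY is estimated by regression of the QALY on arm, baseline EQ-5D and age stratum;
- the incremental cost is estimated by regression of total cost on arm and age stratum;
- the incremental result and its interval are built from these adjusted differences, for example by bootstrapping the two regressions together.

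If an existing analysis plan already adjusts in this way, the change only brings the protocol into line with it.

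The cost is a sentence or two of text and a few lines of code, with no new data. The one small downside is missing baseline EQ-5D. Under the two-point area under the curve those women lack a calculable QALY in any case, so adjustment loses nobody further. If only the 18-month value enters, the plan must say how a missing baseline value is handled so that these women stay in the analysis.

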#### *National registries, clinical database and medical records*

Clinical, prognostic and treatment factors will be obtained from the Danish Breast Cancer Cooperative Group (14). In order to develop cost-utility analyses, use of health services

including all outpatient visits to any healthcare clinic will be obtained from the local municipality rehabilitation centers, the Danish National Patient Registry (15) and medical records while information on disability and productivity loss (sick leave, disability pension and retirement pension) will be obtained from the Integrated Database for Labor Market Research (16). Further, information on national health service cost will be obtained from DRG costs from Statens Serum Institute. We will obtain information on disease characteristics (stage and tumor characteristics) and treatment (hospitalization, treatment type, municipality-based rehabilitation and dates for these) on their breast cancer as well as other diseases (diagnosis and date).

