**Figure 3. Percentage of women changing from cases to non-cases in intervention and control group**

| Control group (%) | Intervention group (%) |
|-------------------|------------------------|
|-------------------|------------------------|

|                         |    |    |
|-------------------------|----|----|
| Distress ( $\geq 7$ )   | 61 | 90 |
| Anxiety ( $\geq 8$ )    | 53 | 80 |
| Depression ( $\geq 8$ ) | 44 | 49 |

Conservatively, we expect slightly lowered differences in change from case to non-case in the large full-scale study (20 %), compared to those observed in the pilot study (30%).

In a 2-year period, we expect 948 women to fulfill the inclusion criteria. With an expected participation rate of 80% (85% was reached in the pilot study) 758 will participate. Of these 43% will have high distress (N=324) and will enter the RCT. 57% will have low distress (n=432) and will be invited to participate in observation group who will fill-out questionnaires.

Due to a large number of planned analyses in the RCT study, we assume a highly conservative alpha to be 1%. Within a 2-year inclusion period, we will include 324 patients and an estimated 20% will drop-out or have missing data, resulting in final sample of 260.

With 130 women in each group, an expected 61% women move from cases to non-cases on distress in the control group and 81% percent women move from cases to non-cases on distress in the intervention group, we will obtain 84% power. Similar calculations for anxiety and depression reveals power of 78% and 76%.

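### Carrying the last observation forward is unsuited to EQ-5D, measured only before surgery and at 18 months; costs and QALYs should be estimated on one set of women with missing EQ-5D multiply imputed

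*Protocol*

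**What the plan says.** Under Statistical Analyses, the Protocol plans a cost-utility analysis with QALYs based on EQ-5D, in which "mean differences in costs (health care +disability + productivity loss + intervention) are compared with mean differences in health consequences". The same section sets analysis by intention to treat for everyone in the trial. It also states, without exempting any outcome, that in sensitivity analyses "imputations of missing data will be performed using the last-observation-carried-forward method". No other method for missing data is named.

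The cost inputs are described under National registries, clinical database and medical records, in the sentence that begins "In order to develop cost-utility analyses, use of health services". Service use is drawn from municipal rehabilitation centres, the national patient register and medical records; disability and productivity loss from a labour-market register; and unit costs from DRG tariffs.

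In Figure 2 (Data collection instruments), EQ-5D is marked at baseline and 18 months only. The distress thermometer (DT), GAD-7, PHQ-9 and FACT-B are marked at baseline, 6, 12 and 18 months as well as at the screening visits. Follow-up forms are electronic and reached by an e-mailed link (Questionnaires). Power and participation expects that "we will include 324 patients and an estimated 20% will drop-out or have missing data, resulting in final sample of 260".

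**The concern.** The two halves of the cost-utility result have different chances of being complete. A woman who ignores the 18-month link can still have register and record costs, but she has no utility after baseline. The mixed models planned over all follow-ups do not help, because EQ-5D has one follow-up.

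The only stated remedy fits this outcome badly. For an outcome measured repeatedly, carrying forward at least uses a recent value. For EQ-5D, the only earlier value was taken before surgery, in women selected for a distress score of 7 or more. The Protocol itself expects many of these women to improve: 61% of controls and 81% of the intervention group are assumed to stop being distress cases. Zero change for every missing woman sits poorly with that expectation.

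The economic result is not incidental. It is the subject of the fourth planned paper, and under Perspectives promising cost-effectiveness is one condition for offering the programme to other Danish breast cancer departments.

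**Working it through.** **1. Expected loss.** The Protocol gives 324 randomised and 20% lost. 324 × 0.80 = 259.2, which agrees with the stated 260. The remainder is 324 − 260 = 64, and 64 / 324 = 19.8%. If this general loss applied to the 18-month EQ-5D, and if all of these women still had cost data, 64 would have costs without an observed 18-month utility. Both conditions are assumptions, so 64 is an upper figure for that loss rate.

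**2. Effect of carrying forward.** Let m be the share missing in an arm and Δ the mean EQ-5D change among women with a value. Carrying the baseline forward gives a mean change of (1 − m) × Δ + m × 0. The difference between arms is

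(1 − m_I) × Δ_I − (1 − m_C) × Δ_C,

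which for equal m is (1 − m) × (Δ_I − Δ_C). With m = 0.20 and an assumed true difference of 0.05, this is 0.80 × 0.05 = 0.04, a loss of 20%. The proportion does not depend on the assumed 0.05. If m differs between arms, the arm changes themselves enter as well as their difference, and the error can go either way.

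**3. On the QALY scale.** With equal baselines and straight-line change over 1.5 years, the QALY difference is 0.5 × 1.5 = 0.75 times the 18-month utility difference. So 0.75 × 0.05 = 0.0375 becomes 0.75 × 0.04 = 0.0300, again a 20% loss.

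**4. Choice of women and joint uncertainty.** An illustrative simulation (2,000 trials of 324 women) used assumed true differences of −5 cost units and +0.030 QALY, with about 19% EQ-5D non-response that rises with cost. None of these settings comes from the Protocol.

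| Approach | Cost difference | QALY difference | Correlation of the two |
|---|---|---|---|
| Complete data | −5.0 | +0.030 | −0.69 |
| Responders for both | −4.3 | +0.026 | −0.67 |
| All for cost, responders for QALY | −5.0 | +0.026 | −0.55 |
| All for both, QALY imputed from arm and cost | −5.0 | +0.030 | −0.64 |

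Imputation recovers the QALY difference here partly by construction, since non-response depended only on cost and cost was in the imputation model. The table shows two things. Non-response related to cost can bias the QALY difference even when costs are complete. The joint behaviour of the two differences can be obtained under every approach.

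**The case against.** Much can be said in the Protocol's defence.

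- Carrying forward is confined to sensitivity analyses, so it does not determine the main result. This stands and limits the weight of the point. A sensitivity analysis should still probe the missing-data assumption, and this one mainly pulls the difference towards zero. If only post-baseline values may be carried, EQ-5D has none and the analysis adds nothing.
- The economic analysis set, the imputation model and the resampling scheme are commonly left to an analysis plan, which is not at hand. This also stands, so their absence is not the finding. The finding is that the one method written down does not suit this outcome.
- The 20% covers drop-out or missing data for the power calculation and is not an EQ-5D rate. Cost coverage of all 324 is not assured either: part comes from municipal centres and medical records, the intervention cost has no stated source, and women may withdraw. Hence the wording up to about 64.

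Three stronger readings are tempting and are not supported.

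- A reader might infer that the cost and QALY differences would describe different women. The Protocol names no separate sets and states intention to treat, responders would be a subset of the costed women, and carrying forward would give a value to every woman with a baseline form.
- A reader might infer that joint uncertainty cannot be formed. Cost and EQ-5D belong to the same identifiable women, so resampling women gives it.
- A reader might infer that a confidence interval on a cost-per-QALY ratio is planned, because 99% intervals are promised throughout. The text names no ratio, and an interval for each mean difference would meet that promise.

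**Conclusion.** The point holds in a limited form. By the Protocol's own schedule, EQ-5D has one post-baseline value, and the only missing-data method stated would replace it by a pre-surgery value. At 20% missing in both arms this removes about 20% of any true utility difference, and the same share of the QALY difference. The size rests on three assumptions: the general loss figure applies to the 18-month form, loss is equal between arms, and responders' changes represent the true difference. The number of women with costs but no observed utility is at most about 64 of 324 at that loss rate. The primary distress analysis is unaffected. This is a worthwhile and inexpensive improvement to a secondary analysis that the Protocol intends to use in its advice on implementation.

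**What to change.** In Statistical Analyses, exempt EQ-5D from last observation carried forward. State that incremental costs and QALYs will be estimated on the same set of randomised women. Missing 18-month EQ-5D would be multiply imputed separately within each arm from:

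- baseline EQ-5D and age stratum;
- register costs;
- DT, GAD-7, PHQ-9 and FACT-B at 6 and 12 months, and at 18 months where available.

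Take uncertainty from resampling women with each woman's cost and QALY kept together.

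All these variables are already planned, so no new data collection is needed. The price is a little more analyst time and reliance on a missing-at-random assumption, which the register costs and interim scores make more plausible but cannot prove.
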